## Abstract

**Background:**

After menopause, 10–20% of all women have nearly intolerable hot flushes. Long term use of hormone replacement therapy involves a health risk, and many women seek alternative strategies to relieve climacteric complaints. Acupuncture is one of the most frequently used complementary therapies in Norway. We designed a study to evaluate whether Traditional Chinese Medicine acupuncture-care together with self-care is more effective than self-care alone to relieve climacteric complaints.

**Methods/Design:**

The study is a multi-centre pragmatic randomised controlled trial with two parallel arms. Participants are postmenopausal women who document ≥7 flushes/24 hours and who are not using hormone replacement therapy or other medication that may influence flushes. According to power calculations 200 women are needed to detect a 50% reduction in flushes, and altogether 286 women will be recruited to allow for a 30% dropout rate.

The treatment group receives 10 sessions of Traditional Chinese Medicine acupuncture-care and self-care; the control group will engage in self-care only. A team of experienced Traditional Chinese Medicine acupuncturists give acupuncture treatments.

**Discussion:**

The study tests acupuncture as a complete treatment package including the therapeutic relationship and expectation. The intervention period lasts for 12 weeks, with follow up at 6 and 12 months. Primary endpoint is change in daily hot flush frequency in the two groups from baseline to 12 weeks; secondary endpoint is health related quality of life, assessed by the Women's Health Questionnaire. We also collect data on Traditional Chinese Medicine diagnoses, and we examine treatment experiences using a qualitative approach. Finally we measure biological variables, to examine potential mechanisms for the effect of acupuncture. The study is funded by The Research Council of Norway.

## Background

After menopause, almost two thirds of women experience hot flushes. One third have symptoms persisting up to five years after natural menopause, and 10–20% find symptoms very distressing [1]. Hormone replacement therapy (HRT) is considered the most effective treatment for hot flushes [2]. However, HRT has other biological effects: it prevents fractures and cancer of the colon [3], but increases the risk of breast cancer [4] and thrombo-embolic disease [5]. Based on these data, the Norwegian Medicines Agency revised the guidelines for prescribing HRT in 2003 [6]. Indications are now only hot flushes and urogenital symptoms. HRT should be used for a short time period, in the lowest possible dose, and other strategies should be considered. The reports of adverse events generated considerable public interest in Norway, and sales figures for systemic HRT have decreased by 45 % since 2001 [7]. Moreover, a Scandinavian study conducted among women treated for breast cancer was terminated when the interim analysis showed that HRT was associated with an increased risk for relapse of the disease [8]. A Norwegian cohort study showed that HRT formulations used in Norway are also associated with an increased risk of breast cancer [9]. The data received considerable public attention and we suppose that they enhanced Norwegian women's interest in low risk strategies to relieve their climacteric complaints.

A large body of data already shows that HRT effectively relieves hot flush activity (frequency and severity) by approximately 80% [2]. Estrogen placebo interventions reduce hot flush activity by 20–30% [10]. Selective serotonin reuptake inhibitors (SSRIs) and selective noradrenaline reuptake inhibitors (SNRIs) reduce the number of hot flushes by 50–60% in the short term in some studies [11]. On this basis it has been advocated that clinically relevant interventions must have the ability to reduce hot flush activity by 50% or more [10].

Women may explore other approaches to manage their menopausal symptoms. These include phyto-estrogens such as soy, herbal remedies such as black cohosh and red clover, or vitamin E. There is a lack of good evidence of their effectiveness, and lack of knowledge of drug interactions and of long-term safety [1]. Commonly recommended lifestyle changes include stress reduction, increased fruit and vegetable intake, reduced caffeine and alcohol intake, smoking cessation, and increased physical exercise. The evidence for these is anecdotal, supported in some cases by epidemiological studies but not by intervention trials [12].

Acupuncture is one of the most frequently used complementary therapies in Norway [13], and is considered safe in the hands of competent practitioners [14]. One small randomised trial (n = 24) conducted in a Swedish university clinic showed that hot flushes decreased by 50% among women who received standardized electroacupuncture [15]. A further study (n = 30) by the same group found a trend in favour of acupuncture compared with sham acupuncture for climacteric symptoms [16]. In a small crossover study (n = 10) in hypertensive postmenopausal women, acupuncture was associated with a significant reduction in 'complaints' though not in blood pressure [17]. An uncontrolled study in 11 participants found a mean reduction in flush score from 4.2 to 1.9 [18]. A small RCT (n = 16) found genuine acupuncture more effective than sham-acupuncture, with a 76% reduction in flushes [19]. An unpublished Norwegian case series (n = 18) suggests that individualized Traditional Chinese Medicine (TCM) acupuncture can reduce hot flushes by 77%. The current data are insufficient to make recommendations regarding acupuncture treatment for hot flushes, but sufficient to justify further research.

Two studies of acupuncture for hot flushes published since the development of this protocol yielded conflicting results: one study of 103 participants found no effect on daily flush frequency [20], whereas a second study of 29 participants found a reduction in severity but not frequency of nocturnal flushes [21].

There is common agreement among acupuncturists that a minimum of six treatment sessions are necessary to evaluate treatment effect, and as many as eight to ten sessions are necessary to establish a maximum effect [22]. Continuation of the effect may require repeated, but less frequent, treatments. If symptoms relapse, as little as two to three treatments can be sufficient to trigger the treatment effect again. An acupuncture session usually costs NOK 300, and accordingly a typical series of treatments costs NOK 3000.

In Norway, most acupuncture practitioners use the TCM approach, and about 500 practitioners belong to the professional organisation, NAFO. A woman who seeks a TCM acupuncture practitioner for hot flushes chooses a treatment strategy rather than a single intervention. The practitioner will most likely focus on climacteric complaints and general well being rather than hot flush activity alone. Treatment involves a comprehensive TCM diagnostic procedure and general life-style advice in addition to individualized acupuncture treatment. Acupuncturists generally consider that these elements interact intentionally with each other during treatment and constitute a treatment package, i.e. "acupuncture-care". If the elements are separated, the treatment will not reflect what TCM acupuncturists consider relevant and good quality acupuncture for a given condition.

## Methods/design

The objective of the study is to address a pragmatic question, to compare the effectiveness of two low risk strategies to relieve climacteric complaints in postmenopausal women who seek alternatives to HRT: is individualized TCM acupuncture-care together with self-care more effective at reducing the frequency and severity of hot flushes compared with self-care alone. The study will test acupuncture as a complete treatment package, i.e. including the therapeutic relationship and expectation, and address the important question of the overall effect of acupuncture-care, which is highly relevant to both postmenopausal women and their health care providers. The limitations of other possible control groups are discussed below. The changes that are likely to be experienced by women undergoing acupuncture in this study will not be fully captured by the quantitative measures used, and therefore the study team will collaborate with other investigators who wish to explore these qualitatively. If the study shows that acupuncture-care has a clinically relevant effect on climacteric complaints, the research group will proceed further and apply for funding to perform a placebo-controlled trial to determine the importance of needle insertion in the overall effect of acupuncture treatment. In addition, a positive result will justify a study of the effect of acupuncture in other groups of patients such as women with hot flushes induced by tamoxifen and men undergoing treatment for prostate cancer.

A sub-study is conducted in 70 women who participate in the Tromsø-arm of the study, to investigate effects of acupuncture-care on biological variables. Evaluations take place at baseline and after 12 weeks. It is hypothesized that acupuncture reduces hot flushes by increasing β-endorphin activity in the hypothalamus [15]. Calcitonin gene-related peptide (CGRP) is a potent vasodilator, and may be a proxy for β-endorphin activity [15]. Plasma concentration of CGRP and neuropeptide Y (NPY) increases during a hot flush [23], and the urine excretion of CGRP is reduced parallel to the reduction of hot flushes after acupuncture treatment [15]. The urine excretion of CGRP and NPY will be measured.

Acupuncture can modulate autonomic nerve system activity [24], and central sympathetic activity is considered to influence hot flush activity [25]. Autonomic nerve system function is assessed by measuring heart rate variability [26]. Bone mass density is measured at baseline and after 12 months, to investigate rate of bone loss among women with climacteric symptoms. Evaluations further include measurements of serum FSH and estradiol at baseline and end of intervention, to confirm that the women are postmenopausal.

Participants are recruited to three centres (Tromsø, Oslo and Bergen), by the use of newspaper advertisements and promotion through media coverage. Informed consent is obtained from all participants before randomisation. See eligibility criteria in table 1.

### Randomization

Participants are stratified by centre and thereafter block randomised (random block size) to additional acupuncture or no additional acupuncture. Staff at study headquarters at University Hospital of North Norway (UNN), which is not connected with the study, prepared the randomisation database and acts as a central randomisation service. Each local coordinator (Tromsø, Oslo and Bergen) obtains distance randomisation of included participants.

### Experimental intervention

Traditional acupuncturists, using diagnostic methods according to the principles of Traditional Chinese Medicine, diagnose TCM syndromes associated with the symptoms of menopausal hot flushes. The acupuncturists meet the criteria for membership in the Norwegian acupuncture society, "Norsk Akupunkturforening" (NAFO), and have at least five years experience of practice. There are four practitioners in Oslo, three in Bergen and three in Tromsø. This will ensure that the study tests the effects of TCM acupuncture-care, not the individual practitioner.

The Delphi technique [27] has been used to establish a consensus between acupuncturists regarding the standardized diagnostic criteria and treatment guidelines, as previously successfully used for acupuncture treatment of lateral epicondylitis [28].

After the initial diagnosis, each participant is treated with points selected according to the syndrome diagnosis. The acupuncturists are free to add individualised points to treat other symptoms related to the menopause (i.e. those included on the WHQ such as depression, anxiety, insomnia), but not unrelated symptoms. In addition, acupuncturists can use moxibustion (warmed needles) if indicated. The acupuncture treatment comprises up to 10 treatment sessions over 12 weeks. This period can be extended for 2 weeks to allow for personal circumstances. The minimum treatment defined 'per protocol' is 6 sessions.

The acupuncture-care group is free to use any over the counter (OTC) drugs and self-provided non-pharmaceutical intervention during the intervention period. In addition, they can use soy, specific dietary supplements and herbal medicines.

### Control intervention

The control group is free to use any OTC drugs and self-provided non-pharmaceutical intervention during the intervention period. In addition, they can use soy, specific dietary supplements and herbal medicines.

Many possible control interventions were considered and rejected for a variety of reasons. Standard HRT has been tested many times and its effect is well known, as is the effect of placebo HRT [2,10]. Acupuncture is expected to be somewhat less effective in relieving hot flushes, and in this study we focus specifically on the increasing number of women who deliberately are seeking an alternative to HRT. At present there is no satisfactory placebo for acupuncture. Needles inserted into the skin avoiding acupuncture points and meridians (sham acupuncture) are likely to have some effect [29], and the blunt needles (Streitberger needles) that have been developed are difficult to use [30]. In addition, acupuncturists are generally uncomfortable using placebo-needles. This attitude is likely to influence the interaction between therapist and study participant and may influence study results. In this study we want to evaluate acupuncture as it is practised in Norway.

### Adjunctive intervention: self care

All participants are given an information leaflet on available self-provided care (e.g. soy, herbs, local oestrogen, physical activity, relaxation techniques to treat menopausal symptoms), and they are free to use any of these.

The information leaflet is specially prepared by the project team and is based on an authoritative book [31] and best current advice [12].

### Effect measures

Primary endpoint is mean number of hot flushes per 24 hours measured over a one-week period. The numbers of hot flushes are recorded in a daily diary, and flushes are scored by severity on a scale from of zero to ten. The diary is administered for two weeks during the qualifying period, and for one week after 4, 8 and 12 weeks of the intervention period.

Secondary endpoint is the Women's Health Questionnaire (WHQ), a validated, self-administered instrument containing 36 questions assessing a wide range of physical and emotional symptoms of women in the postmenopausal period [32]. A Norwegian version is available and has been validated linguistically. A psychometric validation of the WHQ will be performed during the study period. The WHQ is administered at baseline and at 12 weeks.

Baseline assessment includes sociodemographic data collected in a manner parallel to the NOWAC study [33], medical and gynaecological history, previous experience with acupuncture, which other self-provided and therapist-provided interventions they have used earlier to relieve their climacteric complaints, current use of drugs and dietary supplements, level of physical activity, smoking status and level of alcohol consumption.

At the end of interventions, all participants are asked which other self-provided and therapist-provided interventions they have used to relieve their climacteric complaints during the intervention period.

A hot flush diary and the WHQ are administered to participants in the acupuncture group at 6 and 12 months after the baseline evaluation. The follow up-period allows us to investigate the development of symptoms and the use of symptom relieving interventions after the intervention period (natural course of symptoms and choice of treatment).

At each treatment session the acupuncturists ask specifically about, and record, any adverse events that have occurred during or after the last treatment, and adverse event forms are filled in at 4, 8 and 12 weeks. The women are asked specifically about adverse events in the 8- and 12-weekly diaries.

The excretion of CGRP and NPY in early morning and evening urine samples are measured with a radioimmunoassay method [15], to determine any changes during the intervention period. The measurements are related to serum creatinine.

Heart rate variability measurements are done at baseline and after 12 weeks. After five minutes rest, a ten minutes registration is done with a Novacor Holter-monitor and Holtersoft Ultima software.  Figure 1 shows a  flow diagram of the study design, and the data collection schedule is  detailed in table 2.

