### Statistical power and sample size

Calculations were made in consultation with a professional statistician. The sample size was calculated using NCSS (PASS 2002) programme, using data for hot flush frequency from many previous trials of HRT, herbs and acupuncture. With a baseline daily flush rate of 7.0 (SD 3.0), and assuming that the difference of interest is 20 percentage points (post-treatment flush rates of 3.5 and 4.9 for acupuncture and no acupuncture groups respectively, equivalent to reductions of 50% and 30%, and SD 3.5 for change in flush rate), and employing a two-sided, two-sample t-test for the changes, 100 women in each group were needed to identify a 20% difference with a power of 80% and α-value of 0.05. Assuming a total withdrawal and dropout rate of 30%, we estimated that a total sample size of 286 women is required.

Power calculations for the sub-study of biological variables are based on earlier studies of the CGRP excretion in urine during acupuncture treatment [15]. To identify a supposed 30% difference in CGRP urine excretion with a power of 80% and α-value of 0.05, we need 25–30 participants in each group. To allow for some measurement inaccuracies because CGRP and NYP are to be measured in early morning and evening urine samples, we will use 35 participants in each group.

Data entry is undertaken by the central coordinator, with checking of random 10% samples by the research fellow. Data on primary endpoint are entered by a person not connected to the study team, and who is blinded to treatment allocation.

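### Adverse events are asked about more often, and possibly earlier, in the acupuncture arm, and the week-4 diary is not named as asking about them

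*Protocol article*

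**What the plan says.** The Effect measures section of the protocol article gives three routes by which adverse events reach the trial.

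1. Sessions: "At each treatment session the acupuncturists ask specifically about, and record, any adverse events that have occurred during or after the last treatment". The control arm has self-care only and no sessions, so this route exists in one arm.
2. Forms: "adverse event forms are filled in at 4, 8 and 12 weeks". This clause continues the sentence about the acupuncturists. It names neither the person who completes the form nor the arm.
3. Diaries: "The women are asked specifically about adverse events in the 8- and 12-weekly diaries". This is the only route worded for the participants in general.

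The hot flush diary itself is issued "for one week after 4, 8 and 12 weeks of the intervention period", so a week-4 diary exists but is not listed as asking about adverse events.

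On the number of sessions, Experimental intervention says: "The acupuncture treatment comprises up to 10 treatment sessions over 12 weeks". It adds: "The minimum treatment defined 'per protocol' is 6 sessions". Under Data and safety monitoring, the Steering Group considers reported adverse events at its regular meetings. Data analysis and handling lists no comparison of adverse events between arms.

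**The concern.** Recorded event counts depend on how often, by whom and how early people are asked. One arm is questioned by its own practitioner at each visit. The other is certain to be asked only twice, the first time at week 8. If the true rates were equal, the acupuncture arm would still tend to show more recorded events.

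The second issue is timing. A control who withdraws before week 8 may never have been asked. Her reason for leaving could be an event linked to the self-care products that both arms may use. The Background says that knowledge of drug interactions and long-term safety is lacking for several of these.

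What is at stake is how event rates can be read by the Steering Group during the trial and by readers afterwards. The primary endpoint is not affected.

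**Working it through.** **The plan's own figures.** Statistical power and sample size gives a difference of 4.9 − 3.5 = 1.4 flushes per day, SD of change 3.5, two-sided α 0.05 and power 80%. The normal approximation gives n = 2 × (1.960 + 0.842)² × 3.5² / 1.4² ≈ 98.1, so 99 per arm. The t-test needs 99.1, so 100, as stated. With 30% dropout, 200 / 0.70 = 285.7, so 286, or 143 per arm. These figures reproduce, and the point here does not depend on them except for the 143 and the 30%.

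**Scheduled inquiries per woman over 12 weeks.** Inputs: 10 sessions (maximum) or 6 (per-protocol minimum; some women may attend fewer), 3 forms, 2 diary questions.

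| Reading of the forms | Acupuncture, 10 sessions | Acupuncture, 6 sessions | Control | Ratio |
|---|---|---|---|---|
| Cover both arms | 10 + 3 + 2 = 15 | 6 + 3 + 2 = 11 | 3 + 2 = 5 | 2.2 to 3.0 |
| Cover acupuncture only | 15 | 11 | 2 | 5.5 to 7.5 |
| Not a separate inquiry | 10 + 2 = 12 | 6 + 2 = 8 | 2 | 4.0 to 6.0 |

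On every reading the acupuncture arm is asked at least about twice as often.

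**First scheduled inquiry.** In the acupuncture arm it comes during the treatment sessions. In controls it comes at week 4 if the forms cover them, otherwise at week 8.

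**Controls who leave before any inquiry, if the forms do not cover them.** The document gives no timing of dropout, so even spread over 12 weeks is an assumption.

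- Total at 30%: 143 × 0.30 = 42.9.
- Before week 8: 42.9 × 8/12 = 28.6, about 29.
- Before week 4: 42.9 × 4/12 = 14.3, about 14.
- Between weeks 4 and 8: 28.6 − 14.3 = 14.3, about 14. These are the controls whom a week-4 question would reach.

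Sensitivity to timing: a constant dropout hazard gives 143 × (1 − 0.7^(2/3)) ≈ 30 before week 8 and 143 × (1 − 0.7^(1/3)) ≈ 16 before week 4. Sensitivity to level: with even spread, 10% dropout gives 143 × 0.10 × 8/12 = 9.5 before week 8, and 20% gives 19.1.

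**Effect on an event rate (capture probabilities assumed for illustration only).** Take a true rate of 20% in both arms and 95% capture under acupuncture, which gives a recorded rate of 0.20 × 0.95 = 19%. In controls, capture of 90%, 70% or 50% gives 18%, 14% or 10%. The apparent excess under acupuncture is then 1, 5 or 9 percentage points with no true difference.

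**The case against.** The strongest reply has four parts.

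- **The forms may close the early gap.** Their weeks match the diary weeks, and Data analysis and handling has the headquarters administer all participant evaluation forms. The collection schedule is in table 2, which was not in the text available, and a full protocol may assign the forms by arm. This stands. The early gap in controls is conditional, and silence in a condensed article does not prove it. The imbalance in inquiries remains even if the forms cover everyone.
- **Early events under acupuncture are not missed.** A reader might infer from the diary sentence that early events and early dropouts go unrecorded throughout the trial. The text does not support that, because "At each treatment session the acupuncturists ask specifically about, and record, any adverse events". A small residue remains: each session looks back to the previous treatment, so a woman who stops because of an event after her last attended session has no next session at which to report it.
- **No safety comparison is planned.** A reader might also infer that a stated safety analysis is invalid. None is stated: adverse events are not an endpoint and no test is announced. Closer monitoring of a needling treatment at its sessions is also reasonable in itself. This limits the harm to interpretation, but reported events will still be reviewed and read by arm.
- **A week-8 question may look back.** Its recall period is not given, so women who stay may report earlier events then, subject to memory. It cannot reach women who have already left.

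**Conclusion.** The point holds in a limited form. Ascertainment of adverse events differs by arm on every reading of the text: up to 15 inquiries against 5 at best for the plan, and up to 15 against 2 if the forms are for acupuncture only. Any raw contrast of event rates would lean towards more recorded events under acupuncture.

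If the forms do not cover controls, about 29 of 143 controls have no scheduled inquiry before leaving, about 14 of them gone before week 4. This rests on 30% dropout spread evenly; at 10% to 20% dropout the 29 becomes about 10 to 19. If the forms do cover controls, this gap shrinks to those who leave before week 4.

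The primary analysis and the sample size are untouched. This is a cheap improvement to the safety data and does not correct an error in a stated analysis.

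**What to change.** 1. Put the same adverse-event question, with the same wording and recall period, in the week-4 diary for both arms, as at weeks 8 and 12.
2. Base any between-arm description of event rates only on items asked identically in both arms at weeks 4, 8 and 12. If the forms already go to all women in identical form, say so; they would then count among these items.
3. Report events recorded at sessions separately, as acupuncture-arm data.

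The cost is one more question in a diary already issued and one more sentence in the analysis section. The change would not reach controls who leave before week 4 (about 14 under even spread), but it would reach about as many who leave between weeks 4 and 8, provided they return the diary.

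### Urinary CGRP and NPY are scaled to serum creatinine, which cannot correct for urine dilution, so the sub-study measure as written is not excretion

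*Protocol article*

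**What the plan says.** The Methods/design section of the protocol article sets up a mechanistic sub-study: "A sub-study is conducted in 70 women who participate in the Tromsø-arm of the study". It gives the timing, "Evaluations take place at baseline and after 12 weeks", and the outcome, "The urine excretion of CGRP and NPY will be measured".

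The Effect measures section describes the specimen and assay: "The excretion of CGRP and NPY in early morning and evening urine samples are measured with a radioimmunoassay method". It then fixes the scaling: "The measurements are related to serum creatinine".

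The sub-study size is in Statistical power and sample size. The target is "To identify a supposed 30% difference in CGRP urine excretion with a power of 80% and α-value of 0.05", for which "we need 25–30 participants in each group". The number is then raised to 35 per group, with the reason given as "To allow for some measurement inaccuracies because CGRP and NYP are to be measured in early morning and evening urine samples".

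The article nowhere mentions creatinine measured in urine, a timed or 24-hour collection, a urine volume or any other correction for dilution. It gives no SD for CGRP excretion.

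**The concern.** The amount of a peptide per litre of urine depends on how much is excreted and on how much water it is excreted in. Without a collection time and volume, the second part has to be removed by dividing by something diluted in the same sample. Creatinine in that urine does this, because both concentrations fall together as the urine becomes more dilute. Creatinine in serum does not: it stays nearly constant within a woman whether a given sample is concentrated or dilute.

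The named outcome (excretion) and the stated scaling (serum creatinine) therefore do not fit together. The article names a specific scaling quantity, so this is not a detail left to a fuller document. It can also be carried out as written, since Methods/design has serum drawn at baseline and at the end of the intervention for FSH and estradiol.

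At stake is the sub-study's test of the proposed mechanism. Dilution left in the measure widens the spread of CGRP and NPY values and makes a real 30% difference harder to detect.

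**Working it through.** **1. What each divisor does.** The values here are assumed, for illustration only. Take constant peptide excretion of 100 units/h, serum creatinine of 70 units, creatinine excretion into urine of 0.4 mmol/h, and urine flow of either 0.03 or 0.12 L/h.

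| Quantity | Flow 0.03 L/h | Flow 0.12 L/h |
|---|---|---|
| Peptide concentration | 100/0.03 = 3333 | 100/0.12 = 833 |
| Divided by serum creatinine | 3333/70 = 47.6 | 833/70 = 11.9 |
| Urine creatinine concentration | 0.4/0.03 = 13.33 | 0.4/0.12 = 3.33 |
| Divided by urine creatinine | 3333/13.33 = 250 | 833/3.33 = 250 |

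True excretion is the same in both columns. Dividing by serum creatinine leaves the whole four-fold dilution difference in place; dividing by urine creatinine removes it.

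**2. The plan's own sample size.** Inputs from Statistical power and sample size: difference 30%, power 80%, α 0.05, 25–30 per group needed, 35 per group planned. A two-sided test, 1:1 allocation and a normal approximation are assumed. With no SD given, the 25–30 cannot be reproduced independently. It can only be inverted for the SD it implies, as a percentage of the mean:

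SD = 30 × √(n/2) / (1.960 + 0.842)

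- n = 25: SD = 37.9%
- n = 30: SD = 41.5%

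The t-test version gives 37.1% and 40.8%, so the approximation makes little difference.

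**3. What the rise to 35 buys.** In variance terms it covers 35/30 = 1.17 to 35/25 = 1.40, that is, 17% to 40% extra variance. The largest total SD that keeps 80% power at 35 per group is 30 × √(35/2)/2.802 = 44.8%. The independent added SD that can be tolerated is then:

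- n = 25 basis: √(44.8² − 37.9²) ≈ 24%
- n = 30 basis: √(44.8² − 41.5²) ≈ 17%

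**4. Power for assumed amounts of added dilution SD.** Total SD = √(implied SD² + added SD²). None of the added SDs comes from the document.

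| Added SD (% of mean) | Power at 35 per group (n = 25 / n = 30 basis) | n per group for 80% power |
|---|---|---|
| 0 | 0.91 / 0.86 | 25 / 30 |
| 20 | 0.83 / 0.78 | 32 / 37 |
| 30 | 0.74 / 0.69 | 41 / 46 |
| 40 | 0.63 / 0.59 | 53 / 58 |

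Steps 3 and 4 treat the implied SD as free of dilution noise.

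**The case against.** The best case for the sponsor is that this rests on one word in a condensed article. Serum may be a slip for urine, and the collection procedure may be set out in a document not shown here. The article does not call these spot samples; that is an inference from the absence of any collection time or volume. With a timed collection and recorded volume, excretion would not depend on a creatinine correction. This much stands: the point may turn out to be a wording error. But the word sits in an outcome definition, and nothing else in the article would lead a laboratory or analyst to read it differently.

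The sponsor can also say that the plan foresaw noise in these samples and raised the size to 35 per group to allow for it. That is fair, and with a modest amount of added noise the allowance is enough. What it has to cover is not quantified, so whether it suffices cannot be shown either way.

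The earlier CGRP work behind the calculation may also have included dilution variation in its SD. If so, the table above counts that variation twice, and the planned power already reflects it. The table further assumes that a proper correction adds no noise, although a urine creatinine ratio has variability of its own, and it ignores any gain from combining the morning and evening samples.

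A reader might infer a biased comparison, because self-care advice could alter fluid intake in one arm. The document does not support that: under Adjunctive intervention: self care, the leaflet goes to all participants, and its listed examples do not mention fluids. The Background section does include general life-style advice in acupuncture-care, which leaves a differential change possible but not shown.

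A reader might also infer that serum creatinine adds material kidney-function variation. A divisor that is nearly constant within a woman largely cancels in relative change, so this is minor.

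**Conclusion.** The point holds. As written, CGRP and NPY in urine are related to a quantity that carries no information on the dilution of the sample, and the result is not the urine excretion named as the outcome.

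In a randomised comparison the main consequence is lost precision. Bias requires urine dilution to change differently between arms.

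The size of the loss is not known. On the assumptions that the implied SD of about 38–42% of the mean is dilution-free and that the added noise is independent of it, 35 per group holds 80% power up to an added SD of about 17–24% of the mean and falls below 80% beyond that. It would go too far to conclude that the sub-study is underpowered, because the document gives neither the SD nor the amount of dilution noise.

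The scope is limited to the 70-woman mechanistic sub-study. Hot flush frequency (primary) and the Women's Health Questionnaire (secondary) are untouched.

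**What to change.** In Effect measures, replace serum creatinine with creatinine measured in the same urine sample, and analyse the ratio of CGRP or NPY to urine creatinine. If timed collections with recorded volume are in fact made, say so and define the outcome as excretion per unit time instead. Either version brings the scaling into line with the outcome named in Methods/design.

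The cost is a change of wording and a routine urine creatinine assay on samples already collected, with no added procedure for participants.
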